**Funder**

The NeoVT-AMR project is funded by the Medical Research Council Seed funding Call - Global Maternal and Neonatal Health 2019. Grant reference number: MR/T039035/1.

## Abbreviations

### ABBREVIATION

AE  
AMR  
AR  
CF  
CFU  
CI  
CHG  
COMREC  
CRF  
D  
DM  
DMC  
DMP  
EU  
GCP  
HAI  
IMPAACT

IMP  
IPC  
ISRCTN

ITT  
LMIC  
MHRA

MLW  
MOP  
MRC  
NEC  
NIMP  
OCT  
OHP

PI  
PIL  
PMRA  
RCT  
REC  
SAE  
SAP  
SAR  
SD  
SGUL  
SOP

### EXPANSION

Adverse event  
Antimicrobial resistance  
Adverse reaction  
Consent Form  
Colony forming units  
Chief Investigator  
Chlorhexidine  
College of Medicine Research Ethics Committee  
Case Report Form  
Day  
Data Manager  
Independent Data Monitoring Committee  
Data Management Plan  
European Union  
Good Clinical Practice  
Healthcare Associated Infection  
International Maternal Pediatric Adolescent AIDS  
Clinical Trials Network  
Investigational medicinal product  
Infection prevention and control  
International Standard Randomised Controlled Trial  
Number  
Intention-to-treat  
Low or middle income country  
Medicines and Healthcare products Regulatory  
Agency  
Malawi Liverpool Wellcome Trust  
Manual of Operations  
Medical Research Council  
Necrotising enterocolitis  
Non-investigational-medicinal product  
Octenidine  
Octenidine 0.1% Phenoxyethanol 2% (trade name  
Octenisept Ò)  
Principal Investigator  
Participant Information Leaflet  
Pharmacy and Medicines Regulatory Authority  
Randomised controlled trial  
Research Ethics Committee  
Serious adverse event  
Statistical Analysis Plan  
Serious adverse reaction  
Standard deviation  
St George's University of London  
Standard operating procedure

SmPC  
SSA  
SUSAR  
TMF  
TMG  
UAR  
VT  
WHO

Summary of Product Characteristics  
Site-specific approval  
Suspected unexpected serious adverse reaction  
Trial Master File  
Trial Management Group  
Unexpected adverse reaction  
Vertical transmission  
World Health Organization

## Executive Summary

### Type of research study

This is a factorial randomised controlled pilot trial.

### The problem to be studied

Neonatal infection is a leading cause of morbidity and mortality in low income countries, and rates of antimicrobial resistance in causative organisms are rising rapidly. Strategies to reduce the incidence of neonatal sepsis are urgently required. Early onset neonatal infection (EOS) often results from transmission of pathogenic organisms from labouring mothers to their infants. Application of antiseptic to the genital tract of labouring women and neonates is potentially a cheap, practical, scale-able intervention to reduce transmission of Multi Drug Resistant organisms from mother to child and to reduce EOS, however equipoise exists regarding the effectiveness of such an intervention.

### The objectives

#### Primary outcome measures:

Mothers: change in vaginal and perineal bacterial load (in colony forming units)

Neonates: change in neonatal skin bacterial load (in colony forming units)

#### Secondary outcome measures:

Mothers:

- Maternal toxicity – score and grade (Tolerability and safety)
- Change in neonatal skin bacterial load in neonates exposed to maternal antiseptic, compared to control
- Serious adverse events

Neonates:

- Adapted neonatal skin condition score (safety) (absolute score and grade)
- Temperature (change in absolute temperature and grade (hypothermia))
- Serious adverse events

### Methodology

#### Setting:

Hospital labour ward, postnatal ward and neonatal unit in Zomba Central Hospital in Malawi.

#### Type of participants to be studied:

Women presenting in labour at any gestation with or without rupture of membranes.

Neonates born at a healthcare facility within the last 24 hours, weighing >1000g and not born to enrolled women.

#### Interventions to be compared:

Antiseptic (3 levels): Chlorhexidine (CHG) concentration 1% vs 2% vs 0.1% Octenidine and 2% 2-phenoxyethanol) (OHP) application to vagina and perineum in labouring women or whole body in neonates.

Frequency (2 levels): single application vs multiple application [4 hourly (in mothers) or 24 hourly (in neonates)].

Compared to control groups who will receive normal standard of care.

Randomisation:

Mothers and neonates are each allocated 1:1:1:1:1:1 into 6 intervention arms and 1 control arm. Randomisation is by permuted blocks to guard against bias introduced over time, such as outbreaks of pathogenic bacteria in the hospital.

Both strata:

1% CHG single application

1% CHG multiple application (mothers: 4hrly; neonates: 24hrly)

2% CHG single application

2% CHG multiple application (mothers: 4hrly; neonates: 24hrly)

0.1% OHP single application

0.1% OHP multiple application (mothers: 4hrly; neonates: 24hrly)

Control group

Number of participants:

Within each group of mothers and neonates, 147 individuals will be recruited – 21 per treatment combination or control.

In addition, babies born to participating mothers will have swabs taken and are included in the total participant count. The total sample size will be 441 individuals.

Duration/planned follow-up:

16 months to complete recruitment and follow-up. Final follow up for both groups will be 28 days after enrolment.

**Expected findings**

Trial hypothesis: Topical antiseptic use leads to greater reductions in bacterial colonisation in both mothers and neonates compared to control. Reduction is greater at higher frequency of application and at higher concentration of CHG.

## 1. Background Information

Infection remains a major cause of neonatal mortality, with serious bacterial infection (SBI) responsible for an estimated 680,000 neonatal deaths per year in low income countries (LIC)(1). Gram negative pathogens, such as *Escherichia coli*, and *Klebsiella* spp., are now the most common cause of SBI in many low and middle income countries (LMIC)(2,3). A rise in antimicrobial resistance (AMR) of these pathogens has recently been observed, and it is estimated that resistant organisms are responsible for 30% of all neonatal infectious deaths globally(4). Extended Spectrum Beta-Lactamase producing Enterobacteriaceae (ESBL-E)(5,6) are of particular concern in the African context as access to carbapenems is limited.

The majority of SBI identified in neonates in LICs appears to be early onset sepsis (EOS), occurring within the first 72 hours of life(5,7). A major mechanism of such EOS is through pathogens acquired during birth from the maternal perineum and genital tract – so called vertical transmission (VT) from mother to child(8–11). There is a high frequency of carriage of ESBL-E in healthy individuals in LMIC, ranging from 17- 22% in Africa(12,13) to 46% in the West Pacific region, with a trend towards increasing prevalence over time(13). These data highlight the potential for interventions to reduce vertical transmission of ESBL-E pathogens in neonatal sepsis.

New strategies to reduce SBI in neonates are urgently required. In high-income countries (HIC) intrapartum antibiotics have been used to reduce the risk of mother to child transmission of Group B *Streptococcus* (GBS), however both the logistics of widespread administration in LICs and the diversity of pathogens coupled with the rise in AMR necessitate an alternative solution for LMIC. Antiseptics - which can be used vaginally or applied topically to neonates - are a potential method to reduce VT of resistant pathogens as they are cheap, widely used, generally well tolerated, and easy to administer, even in resource poor settings.

The most widely used antiseptics in maternal and neonatal populations are topical chlorhexidine (CHG), octenidine (OCT) and octenidine 0.1% combined with phenoxyethanol 2% (OHP) (trade name Octenisept®). CHG is routinely used for skin cleaning prior to procedures in neonatal units and has been shown to significantly reduce skin bacterial load for up to 72 hours following application(14,15). OHP is used widely as a treatment for bacterial vaginosis and is used as the routine antiseptic in many neonatal units in Europe(16). Importantly some reports have shown higher activity of OCT against gram negative organisms compared to CHG(17–20).

A large randomised controlled trial (n=8011) of vaginal and neonatal CHG wipes for the prevention of early-onset GBS disease conducted in South Africa from 2004-2006 found no evidence of an effect on culture positive or clinically diagnosed EOS(21). However, this study was conducted 15 years ago when the epidemiology of EOS differed substantially from that observed today and focused on GBS rather than gram negative/drug resistant isolates. In addition, this study took place in a setting with a relatively low incidence of culture positive EOS (3/1000 recruited births), involved a large study team which significantly improved baseline standards of care independent of the intervention, used low concentration of CHG (0.5%), and the majority of labouring women in the intervention arm only received one CHG application(21,22). Large, non-randomised studies of CHG vaginal administration conducted in LIC prior to this trial had reported substantial reductions in infection related mortality in infants(23,24) and a systematic review concluded that intrapartum, vaginal chlorhexidine may reduce neonatal

infection/sepsis but the impact of concentration on outcome was unknown(25). A recent Cochrane review highlighted the lack of evidence for the use of CHG to prevent non-GBS EOS in neonates(26).

Large pragmatic trials are required to investigate whether antiseptic use in neonates and labouring women reduces clinical sepsis in moderate-high incidence settings, particularly with highly resistant organisms. However, equipoise exists surrounding the optimal choice of drug, dosing and scheduling of antiseptic administration and whether maternal or neonatal administration is more effective. This pilot trial aims to investigate the effect of different strategies of topical antiseptic use in labouring women and new-born infants on reducing bacterial load in the female genital tract and on the skin of new-borns. Results from this trial will inform the design of a planned pragmatic clinical trial of antiseptic use to prevent EOS in neonates in LMIC. A complementary trial investigating the optimal antiseptic regime to reduce skin bacterial load in low birth weight (LBW) infants admitted to neonatal intensive care units (NICUs) - designed to inform antiseptic interventions to reduce late onset sepsis and healthcare associated transmission of pathogens in NICUs in Africa and Asia - has been funded as a pilot by the Medical Research Council (MRC – JGHT call, Chief Investigator [name]).

## **2. Rationale of the Research Project**

This trial will identify the optimal antiseptic strategy for labouring women and neonates to be tested in a larger clinical trial of interventions to prevent neonatal sepsis. It is part of a programme of work to identify pragmatic, scale-able interventions that can be used in clinical practice to protect neonates in low income countries from serious infection. Neonatal sepsis has long-term consequences for affected infants, their families and the health care system, with a significant social and economic impact on communities in low income countries. Prevention of neonatal sepsis is therefore a global health priority, reflected in the sustainable development goal (SDG) 3.2 to reduce neonatal mortality to as low as 12/1000 live births(27). This trial is part of a global effort to address the escalating challenge of antimicrobial resistance (AMR). It will provide data to inform antiseptic use to reduce transmission of pathogenic bacteria from mothers to infants, including resistant gram-negative bacteria which are emerging as a major global cause of serious neonatal infections. Recent child mortality surveillance data from sub-Saharan Africa and Asia identified gram negative bacteria as the most common contributory pathogens in neonatal deaths(28).

Potential long-term beneficiaries of this research include neonates and their families, health care workers, and health systems. Results from this trial, and from research leading on from it, will inform public health and infection prevention and control (IPC) strategy at local, national and international levels. This is a clinical trial which will be conducted in the maternity, postnatal and neonatal units of a busy government hospital in a low-income country. It will provide opportunities for education and training on IPC for health care providers and for the families of new-born infants. Follow-up qualitative assessments of the acceptability and feasibility of the interventions will be an integral part of the trial. These will be shared with local clinical teams to support the development of successful, locally appropriate, IPC guidelines.

This pilot trial is one step in a programme of work designed to reduce the burden of neonatal sepsis. A clinical trial is planned to follow on from this trial, and the trial will need to be completed and the results disseminated, before any positive findings could be incorporated into policy.

## 2.1. Research questions

What is the optimal strategy in terms of efficacy and safety of using a topical antiseptic applied to i) the genital tract in labouring women and ii) the skin in newborn infants, to reduce bacterial load?

## 3. Aims and objectives

The broad objective is to assess the optimal regime of choice of antiseptic agent and frequency of application to reduce bacterial colonization in the genital tract of laboring women and skin of newborns. The specific objectives of this pilot trial are:

To assess the efficacy of different antiseptic agents and regimes, in reducing bacterial load when applied to the vagina and perineum of labouring women and the skin of neonates.

To evaluate the safety of administering topical antiseptics to labouring women and to neonates.

## 4. Methodology

### 4.1. Type of Research Study

The experimental approach is a randomised controlled trial. The trial design incorporates two independent strata: labouring women (mothers) and neonates (born to mothers who have not been recruited into the trial). The trial design for each group is a 3x2 factorial plus control arm, which enables efficient comparison of the choice of antiseptic (drug), the concentration (dose) and frequency of application (duration).

### 4.2. Study Place

The research setting is in the labour ward, and the neonatal and postnatal ward in Zomba Central Hospital, Zomba, Malawi.

### 4.3. Study Population

The study will recruit women presenting in labour at any gestation with or without rupture of membranes and neonates born in a healthcare facility within the last 24 hours, weighing >1000g and not born to enrolled women.

### 4.4. Study Period

This study will take 16 months to complete recruitment and follow-up. Final follow up for both groups will be 28 days after enrolment. For full study timelines see below.

|                                        | 2020 |   |   | 2021 |   |   |   |   |   |    |    |    |    |    |    | 2022 |    |    |    |    |    |    |    |    |    |    |    | 2023 |    |    |    |    |    |    |
|----------------------------------------|------|---|---|------|---|---|---|---|---|----|----|----|----|----|----|------|----|----|----|----|----|----|----|----|----|----|----|------|----|----|----|----|----|----|
|                                        | O    | N | D | J    | F | M | A | M | J | J  | A  | S  | O  | N  | D  | J    | F  | M  | A  | M  | J  | J  | A  | S  | O  | N  | D  | J    | F  | M  | A  | M  | J  | J  |
|                                        | 1    | 2 | 3 | 4    | 5 | 6 | 7 | 8 | 9 | 10 | 11 | 12 | 13 | 14 | 15 | 16   | 17 | 18 | 19 | 20 | 21 | 22 | 23 | 24 | 25 | 26 | 27 | 28   | 29 | 30 | 31 | 32 | 33 | 34 |
| Site set up                     |      |   |   |      |   |   |   |   |   |    |    |    |    |    |    |      |    |    |    |    |    |    |    |    |    |    |    |      |    |    |    |    |    |    |
| Essential documents preparation        |      |   |   |      |   |   |   |   |   |    |    |    |    |    |    |      |    |    |    |    |    |    |    |    |    |    |    |      |    |    |    |    |    |    |
| Ethics and regulatory submission       |      |   |   |      |   |   |   |   |   |    |    |    |    |    |    |      |    |    |    |    |    |    |    |    |    |    |    |      |    |    |    |    |    |    |
| IDMC set up                            |      |   |   |      |   |   |   |   |   |    |    |    |    |    |    |      |    |    |    |    |    |    |    |    |    |    |    |      |    |    |    |    |    |    |
| ISF site documentation and preparation |      |   |   |      |   |   |   |   |   |    |    |    |    |    |    |      |    |    |    |    |    |    |    |    |    |    |    |      |    |    |    |    |    |    |
| Trial documentation preparation        |      |   |   |      |   |   |   |   |   |    |    |    |    |    |    |      |    |    |    |    |    |    |    |    |    |    |    |      |    |    |    |    |    |    |
| IMP supply                             |      |   |   |      |   |   |   |   |   |    |    |    |    |    |    |      |    |    |    |    |    |    |    |    |    |    |    |      |    |    |    |    |    |    |
| SIV and green light                    |      |   |   |      |   |   |   |   |   |    |    |    |    |    |    |      |    |    |    |    |    |    |    |    |    |    |    |      |    |    |    |    |    |    |
| Recruitment                     |      |   |   |      |   |   |   |   |   |    |    |    |    |    |    |      |    |    |    |    |    |    |    |    |    |    |    |      |    |    |    |    |    |    |
| Study Close Out                 |      |   |   |      |   |   |   |   |   |    |    |    |    |    |    |      |    |    |    |    |    |    |    |    |    |    |    |      |    |    |    |    |    |    |

## 4.5. Sample Size

The two independent strata each have a factorial design, with an additional control group. Within each stratum, 147 individuals will be recruited – 21 per treatment combination or control. Additionally, 147 babies from mothers in the maternal stratum will also be swabbed at birth.

Recruitment feasibility has been taken into account during the writing of this protocol. Recent audit data (August 2020 – January 2021) in Zomba Central Hospital showed that there were an average of 138 births a week, which is equal to an average of 19 births per day. Rates of caesarean section ranged from 19% to 52%. This indicates that recruitment will be feasible in around 12 months.

The primary endpoints of log colony forming units (CFUs) are widely accepted to be normally distributed. Although all-cause mortality is more relevant, and will be used in the planned future trial, it is not feasible for this pilot due the increased sample size requirements with a binary outcome. High bacterial load (reflected by log CFUs) is associated with increased risk of neonatal sepsis and consequently provides a good balance between relevance to the scientific question and power in a pilot trial.

However, there is very little data on bacterial load in neonates in LMICs. Additionally, bacterial loads are expected to differ across locations complicating interpretation of previous studies. For example, previous studies in neonates have found varying effects of CHG on log colony counts: a decrease from baseline to 24h of 0.2 SD with 1% CHG in Nepal(29) and 2SDs with 2% CHG in the USA(30). Sample size calculations used standard formula with Bonferroni adjustment for multiple testing within arms of frequency and antiseptic. Within each stratum, 147 individuals randomized to 7 treatment groups, 21 participants per group, provides 90% power to detect a difference of 0.82 standard deviations (SDs) between antiseptics (two-sided  $\alpha=0.012$ ) and 0.58 SDs between frequencies ( $\alpha=0.05$ ) (80% power for 0.72 and 0.50 SDs, respectively). This also provides 90% power to detect a difference of 1.01 SD between each antiseptic and control ( $\alpha=0.012$ ), and 0.90 SD between frequency and control ( $\alpha=0.025$ ) (0.88 and 0.79 SDs at 80% power). These expected effects were judged by clinical and statistical members of the team to be sufficient for selecting a treatment regimen for a future trial.

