## 4. Statistical Analyses

Information will be presented in tables and may also be presented graphically to aid interpretation.

Recruitment data will be presented as per standard CONSORT diagrams (4). Baseline data tables will be presented overall. Unless stated, post-baseline data tables will be presented aggregated by antiseptic and by frequency (working days, alternate working days), with SOC presented separately. Variables will also be presented by factorial randomisation or arm if there is difference between randomised groups of  $p < 0.05$ , used as a flagging device for imbalance and expected for 1 in 20 characteristics by chance, with p-values from t-tests of differences between means for numeric variables and chi-squared tests or Fisher's exact test if cell values are small for categorical variables.

Statistical tests will use 95% confidence intervals unless otherwise stated. Associated two-sided p-values will be produced but binary conclusions of significant/not significant will not be drawn. As this is a pilot trial there will be no adjustment for multiple testing, although interpretation of results will take this into consideration.

All analyses will be included in the interim and final reports unless stated. All analyses will be presented by strata separately and not combined.

IQR: interquartile range

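### Protocol 4.5: the alpha of 0.012 for the antiseptic contrasts is not the Bonferroni level for three comparisons (0.0167) and does not yield the printed detectable differences

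*Protocol*

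**What the plan says.** Protocol 4.5 describes the calculation in one sentence: "Sample size calculations used standard formula with Bonferroni adjustment for multiple testing within arms of frequency and antiseptic". The design is "147 individuals randomized to 7 treatment groups, 21 participants per group". It then gives four pairs of detectable differences.

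- Antiseptic against antiseptic, two-sided alpha 0.012: the design "provides 90% power to detect a difference of 0.82 standard deviations (SDs) between antiseptics".
- Frequency against frequency, alpha 0.05: 0.58 SD at 90% power. The 80% values for these first two contrasts are "80% power for 0.72 and 0.50 SDs, respectively".
- Antiseptic against control, alpha 0.012: "90% power to detect a difference of 1.01 SD between each antiseptic and control".
- Frequency against control, alpha 0.025: "0.90 SD between frequency and control" at 90% power. The 80% values for the two control contrasts are "0.88 and 0.79 SDs at 80% power".

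The paragraph does not say how many comparisons produce 0.012, or which standard formula was used. SAP 2.4 repeats the same figures.

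On the analysis, Protocol 4.10.4 assesses main effects by the estimate and 95% confidence interval, between levels of a factor and against control, and mentions no adjustment. SAP section 4 is explicit: "As this is a pilot trial there will be no adjustment for multiple testing, although interpretation of results will take this into consideration".

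**The concern.** The paragraph's other alphas follow the stated method. There is one comparison between the two frequencies (0.05), and two comparisons of a frequency with control (0.05/2 = 0.025). Three antiseptics give three pairs and three contrasts with control, so the same rule gives 0.05/3 = 0.0167. The printed 0.012 is neither that nor 0.05/4 = 0.0125.

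If 0.012 is the intended level, the stated power is too high for the antiseptic contrasts. If it is a wrong number, the differences may be sound and only the alpha needs correcting. The protocol says these detectable effects were judged sufficient for choosing a regimen to take into a later trial, so a reader should be able to tell which error rate and power that judgement rested on. The 95% intervals planned for the analysis add a third level, with no sentence linking it to the sizing.

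**Working it through.** **Inputs (Protocol 4.5).** There are 21 participants per cell and seven cells. Collapsing the 3×2 factorial gives 42 per antiseptic, 63 per frequency and 21 controls. SD = 1, no allowance for dropout.

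**Formulas.** SE = √(1/n1 + 1/n2).

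- t-test: find d so that P(T > t(1−α/2; df)) equals the target power, where T is noncentral t with df = n1 + n2 − 2 and noncentrality d/SE.
- Normal approximation: d = (z(1−α/2) + z(power)) × SE.

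**Step 1. Identify the formula from contrasts whose alpha is not in doubt** (90%/80% power, in SD).

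| Contrast | n | alpha | Printed | t-test | Normal |
|---|---|---|---|---|---|
| Between frequencies | 63 v 63 | 0.05 | 0.58/0.50 | 0.582/0.503 | 0.578/0.499 |
| Frequency v control | 63 v 21 | 0.025 | 0.90/0.79 | 0.902/0.789 | 0.888/0.777 |

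The t-test reproduces all four figures. The normal approximation misses both frequency-versus-control figures.

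**Step 2. Antiseptic contrasts.**

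| Formula and alpha | Between antiseptics, 42 v 42 (printed 0.82/0.72) | Antiseptic v control, 42 v 21 (printed 1.01/0.88) |
|---|---|---|
| t-test, 0.012 | 0.844/0.746 | 1.041/0.920 |
| t-test, 0.0167 | 0.816/0.719 | 1.006/0.886 |
| Normal, 0.012 | 0.828/0.732 | 1.014/0.896 |
| Normal, 0.0125 | 0.825/0.729 | 1.010/0.893 |

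Worked example, normal approximation at 0.012, 42 v 42: SE = √(2/42) = 0.2182, and (2.512 + 1.282) × 0.2182 = 0.828.

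With the t-test at 0.012, all four printed figures are too small. At 0.0167, three of the four match to two decimals; the fourth comes out at 0.886 against 0.88.

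**Step 3. Power at the printed differences (t-test).**

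| alpha | 0.82 | 0.72 | 1.01 | 0.88 |
|---|---|---|---|---|
| 0.012 (stated) | 88.0% | 76.5% | 87.9% | 75.6% |
| 0.0167 (0.05/3) | 90.3% | 80.2% | 90.2% | 79.4% |
| 0.05 (95% intervals) | 96.0% | 90.3% | 96.1% | 90.0% |

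**Step 4. Solve for the alpha implied by each printed figure.** The t-test gives 0.0160, 0.0164, 0.0161 and 0.0176. Allowing for rounding of the printed differences, the ranges are 0.0151–0.0169, 0.0155–0.0174, 0.0154–0.0168 and 0.0168–0.0184. None includes 0.012. The first three include 0.0167, and the last begins just above it.

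**Step 5. The 0.88.** Rounding alpha to 0.017 gives 0.884, which prints as 0.88. The same formula then puts the 90% values at 0.815 (0.8147 before rounding, so 0.81) and 1.004, slightly off the printed 0.82 and 1.01. The 0.88 therefore needs a recheck, but it is not shown to be an error.

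**The case against.** The protocol says only that a standard formula was used. With the normal approximation at 0.012, the printed antiseptic differences are short by at most 0.016 SD, and power is 89.4%, 78.4%, 89.7% and 78.3%, all within two points of the claim. At 0.0125 that formula matches both 90% figures to rounding. The count of three comparisons is nowhere stated, and the fit at 0.0167 is not perfect. These points stand, and they make 0.0167 a reconstruction. They do not rescue 0.012: the normal approximation fails the paragraph's own frequency-versus-control figures, and at 0.0125 it still misses both 80% antiseptic figures.

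A reader might go further and infer the following, which the documents do not support.

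- *The trial is underpowered.* The 95% intervals planned in Protocol 4.10.4 correspond to more power than stated for the antiseptic contrasts, about 96% and 90%. The planned analysis is also a baseline-adjusted repeated-measures model, so its power differs from any two-sample figure.
- *The stated power belongs to tests that nobody will run.* The frequency contrast is both sized and analysed at 0.05.
- *Adjusted intervals are required.* This is a pilot. SAP section 4 declines adjustment openly, says interpretation will take multiplicity into account, and avoids significant/not-significant conclusions. That is a defensible choice.
- *Error control across every contrast in a stratum has been lost.* Protocol 4.5 adjusts only within each factor, so control over the whole set was never claimed.

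**Conclusion.** The stated pairing of alpha and power for the antiseptic contrasts is wrong as written. If 0.012 is the level, the detectable differences are understated by 0.024 to 0.040 SD under the t-test, and power at the printed values is about 88% and 76%. If the differences are right, the alpha should be close to 0.0167. The second explanation is the more likely, because it follows the paragraph's own Bonferroni pattern and, with one formula, returns seven of the eight printed differences. The documents cannot show whether 0.012 is a misprint.

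The conclusion rests on two assumptions: three comparisons per antiseptic family, inferred from the three antiseptics, and the t-test, inferred from the frequency figures. Under the normal approximation the discrepancy falls to at most 0.016 SD.

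Separately, the protocol does not say that the Bonferroni level served only for sizing. At 95% intervals the familywise control implied by that level is not applied: for the three antiseptic pairs, the chance of at least one false positive is about 12%. This is a point to state plainly, and not a fault in the analysis. The sample size and allocation are unaffected.

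**What to change.** In Protocol 4.5, replace 0.012 by 0.0167 (0.05/3) in both places, name the formula and the number of comparisons, and recheck the 0.88 SD (0.886 at 0.0167, 0.884 at 0.017). If 0.012 is intended, keep it, restate the antiseptic differences as 0.84/0.75 SD between antiseptics and 1.04/0.92 SD against control, and give the number of comparisons that leads to 0.012. Carry the same correction into SAP 2.4.

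Add one sentence to Protocol 4.10.4 saying that the Bonferroni level was used for sizing only and that contrasts are reported with unadjusted 95% intervals. Adjusted intervals beside these are optional.

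The cost is a few numbers and a sentence or two, with no change to recruitment, allocation or the model.
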